| Data/ Statistical Analysis For all parts of the study, the population will be people with new-onset type 2 diabetes in CPRD from 2006 (see section K, above) and the exposure will be ethnicity (either South Asian vs. European [baseline] or African Caribbean vs. European [baseline], as detailed in section L, above). Covariates in base models will include age and sex, and further covariates will be considered individually, as outlined in section vi) below. Statistical analysis is further considered by objective:   1. **Outcome**: time to initiation of first-line anti-diabetic medication, probability of receiving anti-diabetic 1 year post-diagnosis   **Entry**: date of type 2 diabetes diagnosis  **Exit**: date of first anti-diabetic prescription (defined by the absence of a prescription for the medication in the previous 6 months’ records), or end of study/ leaving CPRD practice/ death  **Analysis**: summary statistics will be compared by ethnicity using Kaplan-Meier time-to-event analysis (cumulative failure probability in a given time frame by ethnicity, comparison of medians by log-rank test), Cox proportional hazards regression models will be used to adjust for confounding/ investigate potential mediators  **Example effect measure**: hazards ratio (HR) for anti-diabetic prescription   1. **Outcome:** proportions of patients prescribed medication from each anti-diabetic (stratified by first- to third-line treatment), antihypertensive and lipid-lowering class (defined by the absence of a prescription for the medication in the previous 6 months’ records)   **Sub-population:** a) all participants starting first- to third-line anti-diabetic treatment, b) all patients on antihypertensives, or c) all patients on lipid-lowering medication  **Analysis:** proportions receiving each drug will be compared by ethnicity, then logistic regression models will be used to adjust for confounding/ investigate potential mediators  **Example effect measures**: odds ratio (OR) of being prescribed metformin (=1) vs. non-metformin medication (=0) at first stage of treatment, OR of being prescribed sulphonylurea (=1) vs. non- sulphonylurea medication (=0) at second stage of treatment, OR of calcium-channel blocking antihypertensive prescription vs. non- calcium-channel blocking antihypertensive in those on antihypertensive treatment, OR of statin prescription vs. non-statin lipid-lowering medication prescription in those with >10% 10 year cardiovascular risk   1. **Outcome:** proportions of patients prescribed each dose of each anti-diabetic, antihypertensive and lipid-lowering medication, stratified by treatment stage (defined by the absence of a prescription for the medication in the previous 6 months’ records)   **Sub-population:** a) all participants on first- to third-line anti-diabetic treatment, b) all patients on antihypertensives, or c) all patients on lipid-lowering medication  **Analysis: :** proportions receiving each dose of each drug will be compared by ethnicity, then logistic regression models will be used to adjust for confounding/ investigate potential mediators  **Example effect measures**: OR of being prescribed maximum dose (2g daily) vs. sub-maximum dose of metformin, OR of being prescribed atorvastatin 10mg per day vs. higher doses (20mg, 40mg or 80mg)   1. **Outcome:** yearly monitoring rate post commencement of medication from each anti-diabetic (first- to third-line), antihypertensive and lipid-lowering class – i.e. number of times HbA1c/ blood pressure/ blood lipids measured per person-year of follow-up, stratified by year after commencement; may be multiple entry dates per person for different medications   **Entry:** first use of any medications of interest from 2006 onwards  **Exit:** first of; end of strata (e.g. 1 year after medication commencement), end of study/ leaving CPRD practice/ death  **Analysis:** summary statistics will be compared by ethnicity, Poisson regression modelling used to adjust for confounding/ investigate potential mediators  **Example effect measures**: yearly monitoring rate ratios (RRs)   1. **Outcome:** time to medication intensification (up-titration, addition or switching) after detection of sub-optimal control of diabetes, hypertension or blood lipids, or probability of intensification 1 year post-detection of sub-optimal control; may be multiple entry dates per person for different medications   **Entry:** date when sub-optimal risk factor control detected (see section M for how this is defined for each risk factor)  **Exit:** first of; date of anti-diabetic, antihypertensive or lipid-lowering treatment intensification, end of study/ leaving CPRD practice/ death  **Analysis:** summary statistics will be compared by ethnicity using Kaplan-Meier time-to-event analysis (cumulative failure probability in a given time frame by ethnicity, comparison by log-rank test), Cox proportional hazards regression models will be used to adjust for confounding/ investigate potential mediators  **Example effect measures**: cumulative failure probability for each ethnic group 1 year post detection of sub-optimal value, comparison of median survival times using the log-rank test by ethnicity, HRs of intensification stratified by year   1. **Outcome:** influence of deprivation, polypharmacy, multi-morbidity, drug adherence (iv) and v) only), patient engagement with healthcare, diabetes duration and HbA1c on any ethnic differences found in i) to v).   **Entry:** as above for i), iv) and v)  **Exit:** as above for i), iv) and v)  **Analysis:** as above for i) to v)  **Covariates:** smoking status, BMI, deprivation, polypharmacy, multi-morbidity, drug adherence, patient engagement with healthcare, diabetes duration and HbA1c  **Effect measures:** we will observe the degree of attenuation of the ethnic difference effect measure for each outcome when each covariate is inserted in turn to models, and thus evaluate the likelihood of confounding or mediation  Sub-group/ sensitivity analyses  Analyses will be stratified by age group, and changes in guidelines and temporal trends in drug usage will be accounted for by stratifying by time.  Three sensitivity analyses will be performed – all to boost ethnicity ascertainment. Firstly, on the 58% of CPRD participants with linked secondary care data from Hospital Episode Statistics (HES) (19), using ethnicity codes from HES - present in 78% (18). Secondly, on new registrants since 2006, 78% of whom have ethnicity codes recorded (19). Thirdly, on patients from practices in the London area; where previous research indicates ethnicity recording to be approaching 60% (28).  Plans for addressing misclassification and bias  ­Plans for addressing misclassification of diabetes status and ethnicity are given above (see sections K and L respectively).  Selection bias may arise in ethnicity recording, i.e. greater recording for patients from ethnic minorities, and may also vary across time (with greater recording after the introduction of incentives in 2004) and geographically (greater in urban areas with more ethnic diversity (28) than rural ones with less). We plan to address this in three ways, as detailed above under the “sub-group/ sensitivity analyses” heading. NB/ we do acknowledge these approaches may in themselves introduce bias, and thus we will carefully compare baseline characteristics between the sensitivity and primary analysis populations.  Though primary care prescription data are almost entirely computerised, bias may be introduced into the descriptive arms of the study from unrecorded prescriptions issued in secondary care; equally medication started in secondary care and continued in primary care may falsely lengthen times to up-titration. We anticipate little bias in the monitoring outcome, where blood tests and clinical data such as blood pressure (including those recorded in secondary care) are generally automatically entered into notes via specific templates. Additionally, some bias may be present regarding the ascertainment of treatment intensification, where the intervention is non-pharmacological or constitutes referral to another service. Therefore we will also search for codes indicating lifestyle modification advice or referral which are chronologically close to the medication exposure period.  We plan to examine the influence of drug adherence in explaining any associations between ethnicity and prescribing, but this will only be measured by proxy using the proportion of days covered method; we are unable to verify whether prescriptions have been obtained from pharmacies or whether medication has been taken.  Multiple comparisons  As the study will involve multiple comparisons, findings will be interpreted with caution, and attention paid to clinically meaningful effect sizes rather than p values per se. |

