| Technical Summary (Max. 300 words) UK South Asian and African Caribbean people with type 2 diabetes experience worse diabetic control and more cardiovascular complications than the European-origin population; ethnic minority populations without diabetes also experience an excess of most types of cardiovascular disease. Explanations are unclear. Blood pressure and lipid control, crucial to cardiovascular risk reduction for people with and without diabetes, also differ by ethnicity. However, ethnic differences in prescribing for diabetes, hypertension and hyperlipidaemia remain understudied.  Ethnic differences in prescribing anti-diabetic (in people with diabetes), antihypertensive and lipid-lowering medication (in people with and without type 2 diabetes) will be sought, including: i) time to commencement ii) choice of medication, iii) dosage, iv) monitoring and iv) time to intensification (either medication up-titration, addition or class switching) after detection of sub-optimal control.  Primary care electronic medical records will be used. Established algorithms and code lists will define ethnicity, diagnoses and medication use. Data will be analysed using Kaplan-Meier time-to-event methods and logistic, Poisson and Cox regression models (according to outcome), with South Asian or African Caribbean ethnicity as the exposure (baseline category=European). These methods will allow for differences in follow-up time. The potentially confounding or mediating influences of age, sex, smoking, BMI, deprivation, polypharmacy, multi-morbidity, drug adherence, patient engagement and diabetes duration/ HbA1c will be explored. |
| D. Outcomes to be Measured Proportion of people eligible for antihypertensive or lipid-lowering medication who are prescribed the respective medication; Time to first anti-diabetic/ antihypertensive/ lipid-lowering medication prescription; Choice of anti-diabetic/ antihypertensive/ lipid-lowering medication; Dose of anti-diabetic/ antihypertensive/ lipid-lowering medication; Monitoring of anti-diabetic/ antihypertensive/ lipid-lowering medication; Time to anti-diabetic/ antihypertensive/ lipid-lowering treatment intensification. |

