| Objectives, Specific Aims and Rationale Overall aim  To investigate ethnic differences in prescribing for type 2 diabetes in UK primary care.  Objectives  For people of European, South Asian and African Caribbean origin, ethnic differences in the following will be investigated:   1. Proportions of people with: a) incident hypertension started on antihypertensives and b) an elevated 10 year CVD risk score (according to QRISK, ASSIGN, JBS2, Framingham or unspecified risk-estimating equations (26)) being commenced on statin treatment. 2. Time to initiation of first-line anti-diabetic/ antihypertensive/lipid-lowering medication 3. Choice of anti-diabetic (first- to third-line), antihypertensive and lipid-lowering medication 4. Doses used for each anti-diabetic, antihypertensive and lipid-lowering medication 5. Monitoring rate after medication commencement 6. Time to medication intensification (up-titration, addition or switching) after detection of sub-optimal control of diabetes, hypertension or blood lipids   Additionally, we will examine potential confounding or mediating role/s of:   1. Smoking, BMI, deprivation, polypharmacy, multi-morbidity, drug adherence (for objectives v) and vi)), patient engagement with healthcare, diabetes duration and HbA1c (in people with diabetes).   Null hypotheses   1. No ethnic difference in proportions of people started on a) antihypertensives or b) statin treatment will be detected. 2. No ethnic difference in time to initiation of first-line anti-diabetic, antihypertensive or lipid-lowering medication will be detected. 3. Regarding choice of medication: 4. No ethnic difference in the proportions of people prescribed metformin as first-line, or sulphonylureas, DPP4-inhibitors, thiazolidinediones, SGLT2 inhibitors, GLP1 agonists or insulin as second- or third-line diabetes treatment will be observed. 5. No ethnic difference in the proportions of people prescribed ACE inhibitors/ angiotensin-receptor blockers, calcium-channel blockers or thiazide diuretics for hypertension will be observed. 6. No ethnic difference in the proportions of people with ≥10% cardiovascular disease risk who are prescribed lipid-lowering medication will be observed. 7. No ethnic difference in the proportions prescribed the maximum dose of anti-diabetic, antihypertensive or lipid-lowering medication will be observed, and the modal dose for each class will not differ by ethnicity. 8. No ethnic difference in the monitoring rates of anti-diabetic, antihypertensive or lipid-lowering medication will be observed. 9. No ethnic difference in time to treatment intensification (after the detection of sub-optimal control) of anti-diabetic, antihypertensive or lipid-lowering medication will be observed. 10. Associations between ethnicity and prescribing will not be confounded or mediated by smoking, BMI, deprivation, polypharmacy, multi-morbidity, drug adherence, patient engagement, diabetes duration or HbA1c (in people with diabetes).   Rationale  Research indicates that control of diabetes and its allied cardiovascular risk factors is poorer in UK’s minority ethnic groups than in the background white population. Crucially, these discrepancies are likely to contribute to higher rates of heart disease and stroke, in people with and without diabetes, seen in these groups. By examining the associations above, this study seeks to determine whether ethnic differences in prescribing for people with and without diabetes are present, and explanations for them.  It is important to compare prescribing in people with and without diabetes for each ethnic group. Our previous work suggests that diabetes is a much more potent CVD risk factor in people of South Asian and African Caribbean-origin than those of European-origin, and differential prescribing of statins and anti-hypertensives in those with vs. without diabetes is a possible explanation for this.  If ethnic inequalities in prescribing are present, their identification may influence future prescribing recommendations and thus eventually lessen the personal and societal burden of diabetes and cardiovascular disease complications in ethnic minority groups. |

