| Study Background The UK’s largest ethnic minority groups, people of South Asian and African Caribbean descent, are disproportionately affected by type 2 diabetes (1), and most types of cardiovascular disease (2). UKPDS (UK Prospective Study of Diabetes) established the importance of tight blood glucose control in reducing CVD complications (3), but research suggests that glucose control is poorer in UK South Asians and African Caribbeans than Europeans (4, 5), despite their greater prevalence of complications (2). Yet the use of anti-diabetic medication in these groups remains understudied. Blood pressure and lipid control is key in reducing CVD risk in people with and without diabetes (6), therefore we will also examine prescribing patterns for antihypertensives and lipid-lowering medication.  UK guidelines recommend metformin as first-line anti-diabetic therapy, with several choices of further agents before insulin use (7). A recent study has reported on the choice of second-line treatments in CPRD (8; ISAC protocol number 16_267), with some indication that people from ethnic minority groups are less likely to receive newer anti-diabetic drugs. However, the influence of key factors such as diabetes duration and adherence to treatment were not accounted for, and the related questions of monitoring frequency and expediency of appropriate treatment intensification were not studied. Moreover, evidence from smaller primary care databases suggests South Asians and African Caribbeans are less likely than Europeans to receive insulin, and more likely to be on a higher number of oral diabetes drugs (5, 9). UK hypertension guidelines advocate calcium-channel blockers (CCBs) as first-line treatment for African Caribbeans, and ethnic differences in monotherapy are established (10), but little examination of ethnic differences in prescribing exists beyond this. Studies from aggregated primary care data indicate that statins may be under-prescribed in areas with large ethnic minority populations (11, 12), but were limited by analysis at area level.  Delay in anti-diabetic treatment intensification is linked to poorer subsequent control (13), but in spite of the poorer diabetic control in ethnic minority groups, ethnic differences in time to intensification have never been studied. Equally, an absence of research on ethnic differences in intensification of antihypertensives exists (14). However, previous research indicates that African Caribbean people are less likely than their white counterparts to be prescribed statins (15), though it is unclear if this is the case for people with diabetes. Additionally, whilst evidence from CPRD indicates that hypercholesterolaemia with high cardiovascular risk is inadequately treated in people with diabetes (16), scrutiny by ethnicity is lacking. |

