| Sample size considerations Anti-diabetic analyses  Sample sizes as per “feasibility counts” section, see table 1(below) for detectable differences in ethnic difference effect sizes. Corresponding to objective i), the proportion prescribed an anti-diabetic at 1 year post-diagnosis (42%) is taken from Sinclair et al (22) (detectable differences calculated using stpower cox command in Stata). Corresponding to objective ii), proportions prescribed metformin as first-line (73%) and a sulphonylurea as second line treatment (87%) are taken from Wilkinson et al (8) (power twoproportions command). Corresponding to objectives iv) and v), mean monitoring rate (2.45 times per year [extrapolated], assuming a SD of 2) (power twomeans command) and probability of treatment intensification at 1 year (24%) are taken from Khunti et al (23) (stpower cox command).  **Table 1. Detectable ethnic differences in outcomes.**   \| **Outcome** \| **Exposure (ethnicity): N vs. N** \| **Detectable ethnic difference effect sizes at α=0.05, β=0.90** \| \| --- \| --- \| --- \| \| Time from diagnosis to first anti-diabetic prescription \| South Asians vs. Europeans:  10.5K vs. 120.4K \| HR: 1.03 \| \| African Caribbeans vs. Europeans:  4.6K vs. 120.4K \| HR: 1.03 \| \| % prescribed metformin first-line \| South Asians vs. Europeans:  10.5K vs. 120.4K \| Difference in proportions: 1.4% \| \| African Caribbeans vs. Europeans:  4.6K vs. 120.4K \| Difference in proportions: 2.1% \| \| % prescribed sulphonylurea second-line \| South Asians vs. Europeans:  3.0K vs. 34.4K \| Difference in proportions: 2.0% \| \| African Caribbeans vs. Europeans:  1.3K vs. 34.4K \| Difference in proportions: 2.9% \| \| Mean monitoring rate, measurements per person year at risk \| South Asians vs. Europeans:  10.5K vs. 120.4K \| Rate difference: 0.07 \| \| African Caribbeans vs. Europeans:  4.6K vs. 120.4K \| Rate difference: 0.10 \| \| Time from sub-optimal diabetes control to treatment intensification \| South Asians vs. Europeans:  10.5K vs. 120.4K \| HR: 1.04 \| \| African Caribbeans vs. Europeans:  4.6K vs. 120.4K \| HR: 1.04 \| \| Time to antihypertensive initiation \| South Asians vs. Europeans:  7.6K vs. 119.4K \| HR: 1.02 \| \| African Caribbeans vs. Europeans:  3.8K vs. 119.4K \| HR: 1.02 \| \| Proportions of eligible people at high recorded CVD risk receiving statins \| South Asians vs. Europeans:  3K vs. 49K \| HR: 1.15 \| \| African Caribbeans vs. Europeans:  2K vs. 49K \| HR: 1.18 \|   Antihypertensive analyses  Sample sizes as per “feasibility counts” section. Little prior data exists in this area, but we can assume a mean time to measurement of 1 month (with an assumed SD of 1 month), as per guidelines for re-measurement after intensification (24). This would give a detectable ethnic difference in time until first monitoring as 0.04 months for South Asians vs. Europeans (using the power twomeans command in Stata), and 0.06 months for African Caribbeans vs. Europeans. Data from Petersen et al (25) suggest that 21% of those eligible for treatment for hypertension in the UK remain untreated. Adding this proportion to the expected numbers commencing antihypertensives by ethnicity (see feasibility count section), we would expect 119.4K Europeans, 7.6K South Asians and 3.8K African Caribbeans to be eligible for time to antihypertensive initiation analyses.  Lipid-lowering medication analyses  Sample sizes as per “feasibility counts” section. Assuming a mean time to monitoring of 3 months (26) and an SD of 1 month, the detectable ethnic difference in time until first monitoring would be 0.04 months for South Asians vs. Europeans, and 0.06 months for African Caribbeans vs. Europeans (using the power twomeans command in Stata). Chidwick et al reported that 24% of the high risk population received statins (21), equating to detectable ethnic differences in proportions receiving statins of HRs 1.18 and 1.15.  All detectable differences fall below what is likely to be considered clinically significant. |

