| O. Data/ Statistical Analysis For all parts of the study, the population will be people with and without new-onset type 2 diabetes active in CPRD from 2006 (see section K, above) and the exposure will be ethnicity (either South Asian vs. European [baseline] or African Caribbean vs. European [baseline], as detailed in section L, above). Covariates in base models will include age and sex, and further covariates will be considered individually, as outlined in section vi) below. Statistical analysis is further considered by objective:   1. **Outcome:** Proportion of those eligible for primary prevention who are prescribed a) antihypertensives and b) lipid-lowering medication   **Entry:** Date of incident a) hypertension Read code/ raised BP reading or b) elevated 10 year CVD risk score, at least 12 months after study start date of 1^st^ January 2005  **Exit:** First of; date of first antihypertensive/ lipid-lowering medication prescription (defined by the absence of a prescription for the medication in the previous 6 months’ records), end of study, leaving CPRD practice or death  **Analysis:** Proportions receiving antihypertensives/ statin will be compared by ethnicity, then logistic regression models will be used to adjust for confounding/ investigate potential mediators  **Example effect measure:** Odds ratio (OR) of receiving an antihypertensive/ lipid-lowering medication vs. not for each ethnic group of interest, stratified by time period since identification of hypertension/ elevated CVD risk   1. **Outcome**: time to initiation of first-line anti-diabetic/ antihypertensive/ statin, probability of receiving anti-diabetic/ antihypertensive/ statin at one year post-diagnosis/ identification of high CVD risk   **Entry**: date of type 2 diabetes diagnosis/ incident hypertension Read code or raised BP reading/ incident high 10 year CVD risk score recording  **Exit**: date of first anti-diabetic/ antihypertensive/ statin prescription (defined by the absence of a prescription for the medication in the previous 6 months’ records), or end of study/ leaving CPRD practice/ death  **Analysis**: summary statistics will be compared by ethnicity using Kaplan-Meier time-to-event analysis (cumulative failure probability in a given time frame by ethnicity, comparison of medians by log-rank test), Cox proportional hazards regression models will be used to adjust for confounding/ investigate potential mediators  **Example effect measure**: hazards ratio (HR) for anti-diabetic/ antihypertensive/ statin prescription   1. **Outcome:** proportions of patients prescribed medication from each anti-diabetic (stratified by first- to third-line treatment), antihypertensive and lipid-lowering class (defined by the absence of a prescription for the medication in the previous 6 months’ records)   **Sub-population:** a) all participants starting first- to third-line anti-diabetic treatment, b) all patients on antihypertensives, or c) all patients on lipid-lowering medication  **Analysis:** proportions receiving each drug will be compared by ethnicity, then logistic regression models will be used to adjust for confounding/ investigate potential mediators  **Example effect measures**: odds ratio (OR) of being prescribed metformin (=1) vs. non-metformin medication (=0) at first stage of treatment, OR of being prescribed sulphonylurea (=1) vs. non- sulphonylurea medication (=0) at second stage of treatment, OR of calcium-channel blocking antihypertensive prescription vs. non- calcium-channel blocking antihypertensive in those on antihypertensive treatment, OR of statin prescription vs. non-statin lipid-lowering medication prescription in those with >10% 10 year cardiovascular risk   1. **Outcome:** proportions of patients prescribed each dose of each anti-diabetic, antihypertensive and lipid-lowering medication, stratified by treatment stage (defined by the absence of a prescription for the medication in the previous 6 months’ records)   **Sub-population:** a) all participants on first- to third-line anti-diabetic treatment, b) all patients on antihypertensives, or c) all patients on lipid-lowering medication  **Analysis: :** proportions receiving each dose of each drug will be compared by ethnicity, then logistic regression models will be used to adjust for confounding/ investigate potential mediators  **Example effect measures**: OR of being prescribed maximum dose (2g daily) vs. sub-maximum dose of metformin, OR of being prescribed atorvastatin 10mg per day vs. higher doses (20mg, 40mg or 80mg)   1. **Outcome:** yearly monitoring rate post commencement of medication from each anti-diabetic (first- to third-line), antihypertensive and lipid-lowering class – i.e. number of times HbA1c/ blood pressure/ blood lipids measured per person-year of follow-up, stratified by year after commencement; may be multiple entry dates per person for different medications   **Entry:** first use of any medications of interest from 2006 onwards  **Exit:** first of; end of strata (e.g. 1 year after medication commencement), end of study/ leaving CPRD practice/ death  **Analysis:** summary statistics will be compared by ethnicity, Poisson regression modelling used to adjust for confounding/ investigate potential mediators  **Example effect measures**: yearly monitoring rate ratios (RRs)   1. **Outcome:** time to medication intensification (up-titration, addition or switching) after detection of sub-optimal control of diabetes, hypertension or blood lipids, or probability of intensification 1 year post-detection of sub-optimal control; may be multiple entry dates per person for different medications   **Entry:** date when sub-optimal risk factor control detected (see section M for how this is defined for each risk factor)  **Exit:** first of; date of anti-diabetic, antihypertensive or lipid-lowering treatment intensification, end of study/ leaving CPRD practice/ death  **Analysis:** summary statistics will be compared by ethnicity using Kaplan-Meier time-to-event analysis (cumulative failure probability in a given time frame by ethnicity, comparison by log-rank test), Cox proportional hazards regression models will be used to adjust for confounding/ investigate potential mediators  **Example effect measures**: cumulative failure probability for each ethnic group 1 year post detection of sub-optimal value, comparison of median survival times using the log-rank test by ethnicity, HRs of intensification stratified by year   1. **Outcome:** influence of deprivation, polypharmacy, multi-morbidity, drug adherence (iv) and v) only), patient engagement with healthcare, diabetes duration and HbA1c on any ethnic differences found in i) to v).   **Entry:** as above for i), iv) and v)  **Exit:** as above for i), iv) and v)  **Analysis:** as above for i) to v)  **Covariates:** smoking status, BMI, deprivation, polypharmacy, multi-morbidity, drug adherence, patient engagement with healthcare, diabetes duration and HbA1c  **Effect measures:** we will observe the degree of attenuation of the ethnic difference effect measure for each outcome when each covariate is inserted in turn to models, and thus evaluate the likelihood of confounding or mediation  Sub-group/ sensitivity analyses  See section O of original application  Plans for addressing misclassification and bias  See section O of original application  Multiple comparisons  See section O of original application |

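### Time to intensification counts switches without separating step-ups from one-for-one replacements, and the amendment's own texts disagree on which switches count

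*Supplement*

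**What the plan says.** The latest text is the amendment of 9 December 2019 in the Supplement. It describes the intensification outcome in three places.

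- Objectives, objective 6: "Time to medication intensification (up-titration, addition or switching) after detection of sub-optimal control of diabetes, hypertension or blood lipids".
- Section O (Data/Statistical Analysis): "time to medication intensification (up-titration, addition or switching) after detection of sub-optimal control of diabetes, hypertension or blood lipids".
- Technical Summary: "time to intensification (either medication up-titration, addition or class switching) after detection of sub-optimal control".

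Under section O, follow-up starts when sub-optimal control is detected and ends at the first of "date of anti-diabetic, antihypertensive or lipid-lowering treatment intensification, end of study/ leaving CPRD practice/ death". The first qualifying change is therefore the event in both the Kaplan-Meier and the Cox analyses.

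No section says that a switch must raise the number of agents, the dose or the potency. None sets aside switches made for other reasons or reports switches apart from the other components. Section N defines sub-optimal control for each risk factor but does not define a switch. The listed appendices are peer-review outcomes, code lists and the diabetes adjudication algorithm.

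The bias discussion, which the amendment carries forward by reference to the original application, says of this outcome that "some bias may be present regarding the ascertainment of treatment intensification, where the intervention is non-pharmacological or constitutes referral to another service". It also covers medication started in secondary care. It does not mention switches that leave treatment no stronger.

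The amendment's Study Background states that "UK hypertension guidelines advocate calcium-channel blockers (CCBs) as first-line treatment for African Caribbeans".

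**The concern.** There are two problems, and the first needs no assumption. Two programmers working from the same amendment could build different endpoints, because the summary requires a change of class and the objective and section O do not.

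The second is about interpretation. The endpoint is meant to show whether inadequate treatment is stepped up at different speeds in different ethnic groups. If one antihypertensive replaces another, with the number of drugs unchanged, the patient counts as intensified on any of the three texts. If such replacements are more frequent in one group, that group appears to be stepped up sooner; if they are less frequent, it appears to be stepped up later. Adjusting for age, sex and the listed covariates one at a time does not correct an event that mixes two things. The ethnicity-specific guideline gives a reason, in the plan's own words, why replacement in the antihypertensive analyses might depend on the exposure.

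**Working it through.** **Texts side by side**

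| Change after a sub-optimal reading | Objective 6 and section O | Technical Summary |
|---|---|---|
| Dose of the same drug raised | event | event |
| Drug added | event | event |
| One class replaced by another, number of drugs unchanged | event | event |
| One statin replaced by another | event | not an event |
| Dose of the same drug lowered | not an event | not an event |

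Replacing an ACE inhibitor with an angiotensin-receptor blocker is a further unclear case. It is a switch under objective 6 and section O. Under the summary it depends on whether the two form one class, and the amendment's null hypothesis on antihypertensive choice groups them together.

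**The plan's own figure for this endpoint**

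Table 1 gives a detectable hazard ratio (HR) of 1.04 for diabetes intensification in both comparisons. The inputs are 24% intensified at 1 year, groups of 10.5K vs 120.4K and 4.6K vs 120.4K, α = 0.05 (taken as two-sided) and the stated 0.90 read as power. By Schoenfeld's formula, HR = exp[(1.960 + 1.282)/√(D·a·(1−a))], where D is the number of events and a the minority share.

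- South Asian: D = 130,900 × 0.24 = 31,416; a = 0.080; HR = 1.070.
- African Caribbean: D = 125,000 × 0.24 = 30,000; a = 0.037; HR = 1.104.

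The stated 1.04 is not reproduced. It appears only if a 1:1 split is put in (1.037 and 1.038). It is therefore a poor yardstick for the size of any contamination, and it concerns diabetes only. Table 1 has no detectable HR for antihypertensive intensification.

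**Illustration of size (assumed inputs)**

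The documents give no switch rates. Let s be the share of European events that are non-intensifying switches, r the minority-to-European hazard ratio for those switches, and θ the true hazard ratio for step-up. With s, r and θ constant over time:

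composite HR = (1 − s)·θ + s·r

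With no true difference (θ = 1):

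| s | r = 1.25 | r = 1.5 | r = 2 |
|---|---|---|---|
| 5% | 1.0125 | 1.025 | 1.05 |
| 10% | 1.025 | 1.05 | 1.10 |
| 20% | 1.05 | 1.10 | 1.20 |

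In the other direction, with r = 0.5: 0.975 (s = 5%), 0.95 (s = 10%) and 0.90 (s = 20%). For example, 0.80 + 0.20 × 0.5 = 0.90.

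For a true delay of θ = 0.90 to be hidden completely (composite HR 1.00), r = [1 − 0.9(1 − s)]/s:

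- s = 5%: (1 − 0.855)/0.05 = 2.9
- s = 10%: (1 − 0.81)/0.10 = 1.9
- s = 20%: (1 − 0.72)/0.20 = 1.4

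**The case against.** The strongest reply is that the plan deliberately chose a broad outcome. A switch counts only after sub-optimal control has been detected, so replacing a drug at that point may well be a genuine response to poor control. Objective 3 separately compares drug class by ethnicity, including calcium-channel blocker against other antihypertensives, so class differences will be visible. All of this stands, and it is why the composite should be kept. It does not show how much of an ethnic difference in the composite comes from step-up, and it does not settle which switches count.

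Three stronger readings are tempting, and the documents do not support them.

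- **That the endpoint is biased by ethnicity in a known direction.** No switching rates by ethnicity are given. The background also says monotherapy already differs by ethnicity. If many African Caribbean patients start on the recommended class, they have less reason to switch to it, so r could be below 1. The guideline mechanism concerns one drug group and one comparison. Nothing cited extends it to South Asians or to anti-diabetic or lipid-lowering drugs.
- **That any downward statin change is scored as intensification.** Lowering the dose of the same statin is neither up-titration, addition nor switching. A lower dose of a different statin is an event only under the broader wording.
- **That the main event should be restricted to switches that raise the number of agents, the relative dose or statin intensity.** Replacing an oral agent with insulin could fail all three tests and be set aside as mere replacement. The background reports lower insulin use in both minority groups, so that rule could itself misclassify by ethnicity.

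**Conclusion.** The point holds in a limited form. The three texts need reconciling, and that conclusion rests on the wording alone. As planned, the composite cannot tell faster step-up from more replacement switching. A differential effect is possible but not shown, and its direction is not determined.

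For equal true step-up, the distortion is a composite HR of about 1.01 to 1.20 for s of 5% to 20% and r of 1.25 to 2, with the corresponding fall below 1 if r is below 1. A true HR of 0.90 would be hidden if s = 10% and r = 1.9, or s = 20% and r = 1.4. These values of s and r are assumptions, not estimates. A reader might set them against the stated detectable HR of 1.04 and conclude that even slight contamination would be declared significant. That comparison should not be made, because the figure does not follow from the stated group sizes and belongs to the diabetes analysis, whereas the guideline mechanism is antihypertensive.

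**What to change.** 1. Use one definition of intensification in the Technical Summary, objective 6 and section O. It should say whether within-class switches count and, for antihypertensives, which drugs form a class.
2. Keep the composite as the planned outcome.
3. Report up-titration, addition and switching separately by ethnicity, with cause-specific hazard ratios.
4. Add a sensitivity analysis in which the event is up-titration or addition only, and a switch neither counts as the event nor ends follow-up. State how up-titration is judged after a switch, for instance against the dose at which the new drug was started.

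The cost is protocol wording and modest extra coding. Drug and dose are already outcomes under section N, so no new data are needed. The sensitivity analysis will have fewer events, and it will leave out switches that genuinely step treatment up. It should therefore be read beside the composite and not in its place.
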